The importance of addressing this question is further highlighted by the circumstance that many of the countries most affected by the HIV epidemic are also those where women have the fewest contraceptive options available to them, and many rely on DMPA. Further complicating matters are the competing risks women must weigh in settings where forgoing family planning puts them at significant risk of maternal morbidity or mortality.

If the ECHO trial finds higher risk of HIV acquisition among women randomized to DMPA than to either of the comparators without robust evidence available on the potential alternative injectable NET-EN, the negative impact on family planning programmes may result in increased maternal and perinatal mortality from unintended pregnancies. Moreover, the increase in unintended pregnancies may increase women's risk of HIV due to the progestogenic immunosuppressive effects of pregnancy. Observational evidence suggests that HIV risk increases to about 2.8-fold in late pregnancy and 4-fold postpartum^3. Another observational study in South Africa found that pregnant women reported more sexual partners and condomless sex than postpartum women.

Mechanistic hypotheses have focussed on mechanisms whereby DMPA might increase HIV susceptibility, but the opposite is also feasible. On the one hand, DMPA may increase risk due to immunological suppression and hypo-estrogenism. On the other hand, DMPA may reduce

risk by behavioural changes related to reduced libido, increased condom use and amenorrhoea, reducing sexual exposure during menstruation.

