#### Progestin-only injectable (DMPA and NET-EN)

Injectable progestogen contraceptives are acceptable to many women, and have the benefits of convenience, infrequent dosage (every three months for DMPA), confidentiality, a high efficacy rate when used correctly, and their safety for most women, even those with medical conditions or who are post-partum or breastfeeding (and at least six weeks post-partum). However, they have some features that are less desirable for some women, which may lead to discontinuation and unintended pregnancies. The most common side effects include irregular vaginal bleeding, amenorrhea, and weight gain. Additionally, return to fertility can take up to nine months, and the need to attend the health service every two to three months for injections can be inconvenient for women.

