### **6.4 28 Days daily Dairy**

Participating women will be asked to prospectively complete a 28-day daily diary at home of symptoms and behaviour, commencing on the day of their month 6 visit. A daily diary has been used in other studies that measure daily symptoms potentially related to the hormone fluctuations in women. Parameters measured in the daily diary include sexual interest, activity and condom use, mood, and characteristics of menstruation. To optimize compliance and the quality of self-reporting, research staff will show participants how to complete the daily diary by assisting them to complete their 'day 1' entries.

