| Please tell us what happened from mid-day yesterday until mid-day today? |  |                                                                                                                                                                                                                                                                                                                                                                                                       |  |  |  |  |  |  |  |  |  |  |  |  |  |  |  |  |  |  |  |  |  |  |
|                                                                          |  | 
 12345678910111213141516171819202122 
 |  |  |  |  |  |  |  |  |  |  |  |  |  |  |  |  |  |  |  |  |  |  |
| 1 Have you been menstruating?                                            |  |                                                                                                                                                                                                                                                                                                                                                                                                       |  |  |  |  |  |  |  |  |  |  |  |  |  |  |  |  |  |  |  |  |  |  |
| 0=No      2.Light                                                        |  |                                                                                                                                                                                                                                                                                                                                                                                                       |  |  |  |  |  |  |  |  |  |  |  |  |  |  |  |  |  |  |  |  |  |  |

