| 1.Normal    3.Heavy                                                      |  |                                                                                                                                                                                                                                                                                                                                                                                                       |  |  |  |  |  |  |  |  |  |  |  |  |  |  |  |  |  |  |  |  |  |  |
| 2 Has your menstruation been?                                            |  |                                                                                                                                                                                                                                                                                                                                                                                                       |  |  |  |  |  |  |  |  |  |  |  |  |  |  |  |  |  |  |  |  |  |  |
| 0.No menstruation    2.Mild pain                                         |  |                                                                                                                                                                                                                                                                                                                                                                                                       |  |  |  |  |  |  |  |  |  |  |  |  |  |  |  |  |  |  |  |  |  |  |
| 1.Painless menstruation 3.Severe pain                                    |  |                                                                                                                                                                                                                                                                                                                                                                                                       |  |  |  |  |  |  |  |  |  |  |  |  |  |  |  |  |  |  |  |  |  |  |

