| 3 Have you had sexual intercourse?                                       |  |                                                                                                                                                                                                                                                                                                                                                                                                       |  |  |  |  |  |  |  |  |  |  |  |  |  |  |  |  |  |  |  |  |  |  |
| 0.No intercourse if yes 2.Casual partner                                 |  |                                                                                                                                                                                                                                                                                                                                                                                                       |  |  |  |  |  |  |  |  |  |  |  |  |  |  |  |  |  |  |  |  |  |  |
| 1.Steady partner only                                                    |  |                                                                                                                                                                                                                                                                                                                                                                                                       |  |  |  |  |  |  |  |  |  |  |  |  |  |  |  |  |  |  |  |  |  |  |
| 4 If yes Q4 sexual intercourse? Was condom used?                         |  |                                                                                                                                                                                                                                                                                                                                                                                                       |  |  |  |  |  |  |  |  |  |  |  |  |  |  |  |  |  |  |  |  |  |  |

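### The 28-day diary has no code for a day of mixed condom use, asks about bleeding only as menstruation, and its condom item cites the wrong item number

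*Protocol*

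**What the plan says.** Protocol section 6.4 states the diary's purpose: "Parameters measured in the daily diary include sexual interest, activity and condom use, mood, and characteristics of menstruation". Appendix 1 shows the form. Each column covers one day, mid-day to mid-day: "Please tell us what happened from mid-day yesterday until mid-day today".

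- Item 1, "1 Have you been menstruating", has codes 0 for no, 1 for normal, 2 for light and 3 for heavy.
- Item 2, "2 Has your menstruation been", has codes for none, painless, mildly painful and severely painful menstruation.
- Item 3, "3 Have you had sexual intercourse", separates no intercourse, steady partner only, and casual partner. It does not ask for the number of acts.
- Item 4, "4 If yes Q4 sexual intercourse? Was condom used", has codes 0 for no intercourse, 1 for condom and 2 for no condom.

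The background on injectables says: "The most common side effects include irregular vaginal bleeding, amenorrhea, and weight gain". Section 1, under HIV acquisition, gives as ways in which DMPA may lower risk, besides reduced libido, "increased condom use and amenorrhoea, reducing sexual exposure during menstruation".

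Section 4.2 lists amenorrhoea and sexual activity with condom use among the secondary outcomes. Section 4.1 makes every measure other than estradiol and BDI-II exploratory.

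**The concern.** Three features of the form can lose or distort what the diary is meant to capture.

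1. One condom code has to describe a whole day. When acts on that day differ, neither code is right. Read literally, the question invites a yes as soon as one condom was used, which hides the unprotected act.
2. The condition on item 4 refers to item 4. The intercourse question is item 3.
3. Bleeding is asked about only as menstruation. A woman with unscheduled bleeding that she does not regard as a period can truthfully answer no.

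The diary is the only instrument shown that places intercourse, condom use and bleeding in the same 24 hours, and so the only one that could speak to the behavioural routes named in section 1. Once completed diaries are returned, a mixed day coded as condom, or a spotting day coded as no, looks the same as a correctly coded day. No analysis can separate them.

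**Working it through.** No figure in the protocol bears on this point, so there is none to reproduce. The check is mainly a comparison of passages.

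**Condom item.** Item 3's first partner code contains the word *only*, which makes sense only if a day may include more than one partner. The form thus allows for days with more than one act, but item 4 has no code for mixed use. The visit interview (section 5.8.5, list after Table 2) does have an intermediate level, *sometimes*, for condom frequency. Partial use was recognised there but not in the diary.

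**Cross-reference.** Item 4 names Q4; intercourse is item 3. This is a plain drafting error. On paper it does little harm, because item 4 has its own no-intercourse code and staff help with the day 1 entries (section 6.4). The Project Summary allows for an SMS version if funds permit, and there a wrong condition could be programmed as written.

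**Bleeding items.** The background puts irregular bleeding first among the common side effects, but no code in item 1 or 2 names irregular bleeding or spotting. The codes of item 1 are not in order of severity (normal, then light, then heavy) and do not match the heavy, moderate, light and none levels of the visit interview. That interview item is also worded as menstruation, so it does not fill the gap.

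**Possible size of the condom error (illustration only).** The protocol gives none of the inputs, so all are assumed:

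- m = share of intercourse days with two acts, 5% to 30%
- p = condom use per act, 0.3 to 0.7
- r = correlation of condom use between two acts on one day, 0 to 0.8
- every mixed day is coded as condom

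Mixed days as a share of intercourse days = 2·m·p·(1−p)·(1−r).

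True share of intercourse days with any unprotected act = (1−m)(1−p) + m·[1 − p² − r·p(1−p)].

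Relative undercount = mixed share ÷ true share.

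| m | p | r | Mixed days | True share | Undercount |
|---|---|---|---|---|---|
| 0.05 | 0.3 | 0.8 | 0.4% | 70.2% | 0.6% |
| 0.20 | 0.5 | 0.8 | 2.0% | 51.0% | 3.9% |
| 0.20 | 0.5 | 0 | 10.0% | 55.0% | 18.2% |
| 0.30 | 0.5 | 0 | 15.0% | 57.5% | 26.1% |
| 0.30 | 0.7 | 0 | 12.6% | 36.3% | 34.7% |

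Third row in full: mixed = 2 × 0.2 × 0.5 × 0.5 = 0.10; true = 0.8 × 0.5 + 0.2 × (1 − 0.25) = 0.55; undercount = 0.10 ÷ 0.55 = 18.2%.

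Over the whole grid the undercount runs from about 0.6% to 35%, and it is zero when m = 0. A range this wide shows that the size is unknown. It does not estimate it. For the bleeding items the protocol does not support even an illustrative range.

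**The case against.** The strongest reply is that harm is possible but not shown. The condom code fails only on days with at least two acts and differing use, and the protocol does not say how common these are. The light code may catch much of the spotting. The wrong item number is a typographical slip with a safeguard beside it. The visit interview, including month 7, records condom use as always, sometimes or never, so mixed users are not invisible. All of these measures are exploratory. Each of these points stands, and together they keep the matter small. They do not remove it: the interview cannot tie condom use to a day or to bleeding, and whether spotting is coded as light or as no is left to each woman.

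Three stronger readings are tempting, and the protocol supports none of them.

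- A reader might infer that the error differs by arm and could reverse the condom comparison. That needs assumed arm-specific rates of multi-act days, assumed behaviour within the day, and every mixed day coded one way. It also looks only at rates per intercourse day and ignores the number of intercourse days, which item 3 does record.
- A reader might infer that amenorrhoea is overstated. Nothing in the protocol says that amenorrhoea is counted from the diary, and the visit interview asks about menstruation separately.
- A reader might infer that a named endpoint is invalid. Neither unprotected acts nor sex during bleeding is a listed outcome, and section 1 speaks of exposure during menstruation, which is what item 1 asks about.

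**Conclusion.** The three form defects are on the page: no code for mixed condom use, a condition that refers to its own item, and bleeding asked about only as menstruation. The exploratory same-day data on condom use and bleeding can therefore be misclassified, to a degree that the protocol does not allow anyone to estimate. The error is zero if no woman has more than one act in a day and women code spotting as light. The illustrative range above rests wholly on assumed inputs. The BDI-II and estradiol comparisons and the sample size are unaffected. This is a cheap improvement worth making because it cannot be repaired after data collection. It is not a threat to the trial's main conclusions.

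**What to change.** Before the diary is used:

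- **Item 4:** *If yes to Q3, was a condom used every time?* with 0 = no intercourse, 1 = every time, 2 = at least once without a condom.
- **Item 1:** *Have you had any vaginal bleeding or spotting?* with ordered codes 0 = none, 1 = light or spotting, 2 = moderate, 3 = heavy.
- **Item 2:** refer to bleeding in the same terms. Otherwise a woman with spotting would report bleeding in item 1 and have only menstruation codes to choose from in item 2.
- **Visit interview (section 5.8.5):** word the menstruation item the same way, so that concept and levels both match the diary.
- Carry the corrected reference to item 3 into any SMS version.

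The cost is rewording a few lines and redoing any translations. No item, visit or analysis is added. There is one real downside: the bleeding data would be less comparable with earlier studies that asked about menstruation, and item 1 would no longer separate menstrual from other bleeding. The revised item 4 still gives no count of acts, but no listed outcome calls for one.
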